##### Dependent variables for objective 1b--inappropriate screening

For this objective, we are interested in whether the intervention results in decreased screening for ABU in catheterized patients. Screening for catheter-associated ABU will be measured by the number of urine cultures collected per days of catheter use. We predict that as healthcare providers become more comfortable with leaving catheter-associated bacteriuria untreated, they will recognize that urine cultures are frequently unnecessary in catheterized patients and thus, order fewer urine cultures. All urine cultures sent to the microbiology laboratory from the study units will be documented, whether positive or negative. We will calculate the number of urine cultures collected per 100 catheter device-days for each unit.

A secondary outcome for objective 1b will be the frequency of use of urinary catheters in hospitalized patients. We will need to track this information, as our intervention may have the unintentional but beneficial effect of causing providers to remove unnecessary urinary catheters. Therefore, we will also calculate the number of catheter device-days per 100 patient bed-days on each unit.

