## Background

Urinary tract infection (UTI) is the single most common hospital-acquired infection, and many cases of nosocomial UTI are associated with an indwelling urinary catheter [1,2]. Urinary catheters bypass normal host defenses, and bacteriuria develops at the rate of approximately 5% per day; [3] nearly all individuals (98%) who are catheterized for 30 days or longer will have bacteriuria caused by one or more species of potentially pathogenic bacteria [4,5]. Furthermore, organisms causing catheter-associated urinary tract infection (CAUTI) are frequently resistant to one or more antibiotics [6,7]. In addition to these concerns regarding quality of care, annual incremental costs attributed to nosocomial CAUTI in 2002 were estimated to exceed $451 million [8]. Finally, since public reporting of nosocomial infections has become mandated in more than 30 states, [9] hospitals have strong incentive to reduce their rates of hospital-acquired CAUTI.

An important distinction exists between CAUTI and asymptomatic bacteriuria (ABU). CAUTI, as defined by the US Centers for Disease Control (CDC) and the National Healthcare Safety Network, involves symptoms (fever, urgency, frequency, dysuria, or suprapubic tenderness), in addition to microorganisms in the urine [10]. CAUTI requires antimicrobial treatment to relieve symptoms, while patients with ABU are, by definition, asymptomatic. Treatment of ABU in patients with an indwelling catheter does not improve morbidity or mortality, nor does it decrease the incidence of symptomatic CAUTI [11]. Use of antimicrobial agents to prevent or to treat catheter-associated ABU does lead to emergence of resistant flora, however [12]. Accordingly, evidence-based guidelines concerning ABU have stated that it is inappropriate to screen for or to treat ABU associated with the presence of a urinary catheter, with the exceptions of pregnant women and persons undergoing invasive urologic procedures [11,13]. The CDC campaign to prevent antimicrobial resistance in hospitalized patients likewise instructs clinicians to "treat infection, not colonization." [14] Unfortunately, a significant translation gap between evidence-based guidelines concerning management of ABU and clinical practice has been observed throughout the world [15,16]. Overtreatment of ABU is a quality, safety, and cost issue, particularly as unnecessary antibiotics lead to emergence of resistant pathogens [14,17].

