#### Outcomes

Objective 1 focuses on the clinical outcomes of inappropriate screening for and treatment of catheter-associated ABU, as well as on complications of inappropriately prescribed antibiotics (Table 3). Objective 2 focuses on measuring changes in knowledge and attitudes concerning the ABU and CAUTI guidelines (see Table 2).

**Table 3 T3:** clinical outcomes for objective 1 in order of importance

Outcomes	**Measurement of change**^**a**^
Inappropriate treatment of CAABU	Fewer episodes of CAABU treated inappropriately

Inappropriate collection of urine cultures from patients with CAABU	Decreased number of urine cultures/1,000 catheter-days

Number of days antibiotics given for CAABU	Fewer days of antibiotic use for CAABU

Use of urinary catheters	Decreased urinary catheter-days/patient bed-days

Complications of inappropriate antibiotics	*Clostridium difficile *colitis, emergence of resistant organisms^b^

Complications of bacteriuria	No increase in pyelonephritis or urosepsis

^a^Comparisons are for the specific wards on the intervention facility and the corresponding wards on the control facility. ^b^In 30 days following inappropriate antibiotic use in a given patient.

CAABU = catheter-associated asymptomatic bacteriuria.

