### Data collection

#### Surveillance of target hospital wards

Surveillance of all targeted hospital wards will include regular, systematic chart reviews of medical and nursing notes to identify each patient with a urinary catheter, each urine culture ordered on those patients, and the ordering of antibiotics after urine culture results are reported. Research personnel have been trained to follow a systematic process of documentation for each of these measures (described in Table 3), which has been validated against bedside observation.

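### Objective 1b is named inappropriate screening but counts every urine culture per catheter-day, so a fall in that rate cannot by itself show less inappropriate screening

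*Protocol article*

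**What the plan says.** All references are to the protocol article.

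- **Name of the outcome.** Table 3 (Outcomes) lists it second in order of importance, as "Inappropriate collection of urine cultures from patients with CAABU".
- **Measure.** Under Dependent variables for objective 1b: "Screening for catheter-associated ABU will be measured by the number of urine cultures collected per days of catheter use", and "We will calculate the number of urine cultures collected per 100 catheter device-days for each unit". Table 3 gives the direction of success as "Decreased number of urine cultures/1,000 catheter-days". The two places differ in scale (per 100 and per 1,000) but describe the same quantity.
- **What the protocol treats as not inappropriate.** The Background defines CAUTI as symptoms together with organisms in the urine and says that it needs treatment. It calls screening for catheter-associated ABU inappropriate "with the exceptions of pregnant women and persons undergoing invasive urologic procedures". The objective 1b section predicts only that providers will come to see that "they will recognize that urine cultures are frequently unnecessary in catheterized patients and thus, order fewer urine cultures".
- **Classification.** Under Patients participating in the study, symptoms and comorbidities are recorded for each episode of bacteriuria, and each episode is classified as ABU or CAUTI. No such record is described for negative cultures.
- **Regression outcome.** Analyses for objective 1 adds a patient-level logistic model of whether a catheterized patient was screened for ABU. The article does not say how that differs from having had a culture.
- **Safety.** Table 3 includes no increase in pyelonephritis or urosepsis. Dependent variables for objective 1a sets a 30-day follow-up after each bacteriuria episode.

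**The concern.** The outcome's name makes a judgement about each culture that its measure does not make. A culture taken because a catheterized patient has symptoms, or one falling under the Background exceptions, enters the numerator exactly as a screening culture does. Two things follow.

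1. **Interpretation.** A lower rate could reflect fewer screening cultures, fewer indicated cultures, or both, and the measure cannot tell which.
2. **Dilution.** If providers change only their screening, the unchanged indicated cultures make the observed effect smaller than the true one.

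The control site does not settle the first point. Audit and feedback is given only at the intervention site, so any loss of indicated cultures that it caused would appear in the between-site difference.

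**Working it through.** **Objectives 1a and 1b side by side.** For 1a, the diagnostic algorithm sorts each episode before it is called inappropriately managed. For 1b, no described step sorts a culture by indication before it is counted.

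**The plan's own figure.** Estimated sample size for objective 1b claims 80% power for a 25% reduction in the percentage of catheterized patients screened, from as low as 10%, with 1,867 patients at the intervention site and 1,512 at the control site. I read 25% as relative, so 10% falls to 7.5%. With a two-sided 5% test and independent patients:

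- pooled proportion = (1,512 × 0.10 + 1,867 × 0.075) / 3,379 = 0.0862
- SE under the null = √[0.0862 × 0.9138 × (1/1,512 + 1/1,867)] = 0.00971
- SE under the alternative = √(0.09/1,512 + 0.069375/1,867) = 0.00983
- power = Φ[(0.025 − 1.96 × 0.00971) / 0.00983] = 72.8%

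A one-sided test gives 82.1%; sidedness is not stated for 1b. The point made here does not depend on this figure. It also concerns patients screened, not cultures per catheter-day, so the 25% below is only a convenient reference size.

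**Dilution.** Let *s* be the share of counted cultures that are indicated. The documents do not give it, so I assume 10% to 75%. If non-indicated cultures fall by 25% and indicated ones do not change, the observed fall is 25% × (1 − *s*).

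**Fall from lost indicated cultures alone.** If non-indicated cultures do not change, a 25% fall in the total requires a fraction 0.25/*s* of indicated cultures to disappear.

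| *s* | Observed fall after a true 25% cut in non-indicated cultures | Fraction of indicated cultures lost to give a 25% fall |
|---|---|---|
| 10% | 22.5% | not reachable (0.25/0.10 = 2.5) |
| 25% | 18.75% | all |
| 50% | 12.5% | half |
| 75% | 6.25% | one third |

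**Patient-level model, if being screened means any culture.** Take a 10% base rate, let *s* be the share of cultured patients whose culture is indicated, and use the two-sided formula above. Power for a true 25% cut in non-indicated cultures is then 63%, 48%, 24% and 9% for the four values of *s*. Counting only non-indicated cultures would give 68%, 60%, 43% and 24%.

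**Reach of the safety outcome.** The 30-day follow-up starts from a bacteriuria episode, and a culture must first find that episode. A symptomatic patient who is never cultured does not start the follow-up.

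**The case against.** **The rate is a proxy.** Ordering a culture is the behaviour that 1b targets. A total rate counts all of it, negative cultures included, and needs no judgement by research staff. An ABU-positive rate would lose negative screening cultures and would depend on bacteriuria prevalence and on classification. This stands, and it is why the total rate should stay. It does not justify the name.

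**Dilution is conservative.** That is true if indicated cultures are stable, but stability is what the measure cannot show.

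**The regression outcome may be defined more narrowly in the full protocol.** This is possible, so the criticism of that model is conditional. The rate itself is fixed in two places in the article.

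**Harm is monitored separately.** It is, at both sites. The safeguard is real but partial, for the reason given in the working.

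**Stronger readings that the documents do not support:**

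- *Cultures from non-catheterized patients enter the numerator.* A reader might infer this from "All urine cultures sent to the microbiology laboratory from the study units will be documented, whether positive or negative". But being documented is not being counted. The objective 1b section and the logistic model both concern catheterized patients, and Surveillance of target hospital wards limits collection to "each urine culture ordered on those patients".
- *The protocol expects catheter-days to fall.* It says only that the intervention may have this effect.
- *The protocol calls every culture inappropriate.* It does not; it says that cultures are often unnecessary.

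**Conclusion.** The outcome's name claims more than its measure can show. A fall in all urine cultures per catheter-day shows lower culture use. It does not by itself show less inappropriate screening. The same holds for the logistic outcome if screened means any culture.

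The size is unknown because *s* is not given. Over the assumed 10% to 75%, a true 25% cut in non-indicated cultures shows as a fall of 22.5% to 6.25%. A 25% fall made up wholly of lost indicated cultures is possible only if *s* is at least 25%.

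That cultures in symptomatic patients are indicated rests on inference from the CAUTI definition and the wording about cultures often being unnecessary; no sentence states it outright. A reader might go further and conclude that the intervention will suppress needed cultures, or that the measure must be discarded. Nothing in the article shows either.

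**What to change.** 1. Keep the total culture rate in catheterized patients as the 1b measure, label it urine-culture use, and express it on one scale throughout.
2. Report beside it, by site and period, two rates from the classification already made for each bacteriuria episode: ABU-classified positive cultures per 1,000 catheter-days, leaving out the Background exceptions, and CAUTI-classified positive cultures per 1,000 catheter-days as a balancing measure.
3. Conclude that inappropriate screening fell only if the total and ABU-classified rates fall without a matching fall in the CAUTI-classified rate.
4. State what being screened means in the logistic model. If it means any culture, label that outcome as culture use too.

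The cost is a change of wording and two extra rates from the existing database. The downside is that negative cultures cannot be classified from the data described, so they appear only in the total rate. The two classified rates also depend on how consistently episodes are classified across sites and years.

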##### Estimated sample size for objective 1a--inappropriate treatment

We have estimated the sample size of episodes of bacteriuria needed at each of the two sites based on testing the differences in two independent proportions. The effect size to be detected is *h *= | φ_1 _- φ_2 _|, where φ = 2 arcsine √P [39]. Preliminary analyses found that the percentage of patients who received inappropriate treatment was 36%. Assuming a two-sided test, α = .05, and power of 80%, a sample size of 300 episodes is needed at each site in order to detect an 11% reduction in inappropriate treatment at the intervention site (down to 25%) compared to the control site rate of 36%. Specifically, *p*_1 _= .36, φ_1 _= 1.287, *p*_2 _= .25, φ_2 _= 1.047, and *h *= .24, which represent a small effect size. On the specific hospital units targeted in this study, there were over 3,000 discharges associated with urinary catheterization from the study wards at the two sites combined in fiscal year (FY) 2008. Thus, we should have adequate power to detect differences between the intervention and control sites. For the medicine units alone, we will have enough power to detect whether there was a difference in inappropriate treatment between intervention and control sites because there were approximately 1,600 patients at the Houston site estimated to have had catheters in the non-ICU medical bed sections in FY2008 and 1,300 unique patients in San Antonio.

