## Methods

### Study design

The study uses a controlled pre/post design to test an intervention using audit and feedback of healthcare providers to improve their compliance with ABU guidelines. The intervention and the control sites are two different VA hospitals.

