### Analysis

#### Analysis plan and sample size for objective 1

##### Independent variables for objective 1

For the variables in objective 1, it is important to understand that the intervention is applied to the healthcare providers, but the unit of analysis for the outcomes is episodes of bacteriuria occurring in catheterized inpatients (Table 3). We will account for the correlation that may exist among patients treated by the same healthcare provider in our regression models. The independent variables include age and gender of the patient, duration of catheter use, catheter type, hospital ward and service, types and quantities of organisms found in the urine, number of white blood cells (WBCs) in urine, number of WBCs in the serum, and highest temperature in 24 hours around the time of urine specimen collection.

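### The 80% power for objective 1a at 300 episodes per site belongs to a single-period comparison of two hospitals; the declared controlled pre/post contrast has about 53–56% power at 300 per site per period

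*Protocol article*

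**What the plan says.** - **Design.** *Study design* states: "The study uses a controlled pre/post design". The abstract and Table 1 give 12 months of baseline surveillance at both hospitals before the intervention starts in year 2.
- **Sample size.** *Estimated sample size for objective 1a* is "based on testing the differences in two independent proportions". With a two-sided 5% test and 80% power, "a sample size of 300 episodes is needed at each site in order to detect an 11% reduction in inappropriate treatment", down to 25%, "compared to the control site rate of 36"%. It reports an arcsine effect size h of .24. No period is attached to the 300.
- **Analysis.** *Analyses for objective 1* plans a hierarchical regression with episodes within patients within providers. It reads significance from one intervention parameter and names no period term and no site-by-period term.
- **Correlation.** *Independent variables for objective 1* says: "We will account for the correlation that may exist among patients treated by the same healthcare provider in our regression models". The sample-size paragraph states no allowance for it.
- **Support for adequacy.** The sample-size paragraph cites more than 3,000 discharges with catheterization in fiscal year 2008, both sites combined, and counts of catheterized patients. The unit of analysis is the bacteriuria episode, and no episode count is given.

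**The concern.** There is one hospital per arm. A difference between the hospitals in one period mixes the intervention effect with any difference that was already there. The baseline year exists to remove that, and using it means comparing the change at one hospital with the change at the other. That contrast has four proportions and about twice the variance of the comparison that was sized.

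Equal baselines cannot be taken for granted. *Setting* gives 36.1% as the rate on the intervention-site units, and the sample-size paragraph uses 36% as the control-site rate. No separate control-site baseline is shown.

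Inappropriate treatment heads the list of clinical outcomes in Table 3. If the stated power is carried over to the pre/post contrast, a null result from about 300 episodes per cell could be read as evidence of no effect when the chance of detecting the planned effect was little better than one in two.

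**Working it through.** **Inputs from the document:** p1 = .36, p2 = .25, two-sided α = .05 (z = 1.960), power 80% (z = 0.8416), 300 episodes per site.

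**1. The plan's own figure.**
- φ = 2 arcsin √p gives φ1 = 1.287 and φ2 = 1.047, so h = 0.2398. All match the document.
- n = 2(1.960 + 0.8416)²/h² = 273 per site. A pooled two-proportion formula gives 274, or 292 with continuity correction.
- Power at 300 = Φ(0.2398 × √(300/2) − 1.960) = 83.6%.

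So 300 is adequate, with a small margin, for one comparison of independent episodes between two sites.

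**2. The pre/post contrast.** Assume 36% → 25% at the intervention site, 36% → 36% at the control site, independent episodes and n per site per period.
- *Risk difference.* Variance × n = 3(.36 × .64) + .25 × .75 = .6912 + .1875 = .8787. The single-period value is .2304 + .1875 = .4179, so the ratio is 2.1. At n = 300, SE = √(.8787/300) = .0541 and .11/.0541 = 2.03, giving power 52.9% (53.1% in a simulation of 200,000 runs). For 80%, n = .8787 × (2.8016/.11)² = 570.
- *Arcsine.* Power at 300 = Φ(0.2398 × √(300/4) − 1.960) = 54.6%. For 80%, n = 4(2.8016)²/h² = 546.
- *Logit.* The log odds ratio is 0.523 and variance × n = 3/.2304 + 1/.1875 = 18.35. At 300, SE = √(18.35/300) = .247, giving power 56.2%. For 80%, n is about 526.

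**3. Detectable change at 300 per cell (risk difference).** Try a fall to 21%: variance × n = .6912 + .21 × .79 = .8571, SE = √(.8571/300) = .0534, and 2.8016 × .0534 = .150. The detectable net reduction is about 15 points, against the planned 11.

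**4. Clustering.** The margin in the plan is 300/273 = 1.10, so a design effect above 1.10 takes even the single-period comparison below 80%. The document gives no design effect; the values below are assumptions. Arcsine power at 300 per site, or per site per period:

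| Design effect | Single-period comparison | Pre/post contrast |
|---|---|---|
| 1.0 | 83.6% | 54.6% |
| 1.25 | 75% | 46% |
| 1.5 | 67% | 40% |

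**The case against.** **The arithmetic is right and the sizing matches the written test.** This stands. Every figure in the sample-size paragraph reproduces, and the analysis section also describes a plain comparison between sites. The site-by-period contrast is inferred from the declared design and the baseline year; no analysis text states it. But this moves the problem rather than removing it. If the test is between sites, the baseline year plays no stated part in it and hospital is confounded with intervention. If the intervention parameter is meant to be a change relative to control, the stated power is not its power. Design, sizing and analysis need to agree, and restating the power alone would leave the analysis text out of step.

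**300 is a requirement, not the expected yield.** This also stands. Surveillance covers every patient on the study wards for three years. *Estimated sample size for objective 1b* gives 1,867 and 1,512 catheterized patients in a year; 570 episodes would equal 31% and 38% of those numbers (570/1,867 and 570/1,512). A reader might infer that the study is underpowered. The document does not support that, because it gives no count of bacteriuria episodes. For the same reason it does not support the claim of adequate power, which rests on discharges and patients.

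**300 might be the total over both periods.** A reader might split it into 150 per cell and quote power of about 30–32%. Nothing in the text supports that split, since the paragraph requires 300 per site within the comparison it sizes.

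**Clustering detail is often left out of an article.** Fair. The absence of an intraclass correlation is not the point here, and the design effects above are illustrative.

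**Conclusion.** The point holds as a mismatch between the declared design and the stated power, not as a calculation error. The 80% at 300 episodes per site (83.6% when recomputed) is a property of a single-period comparison of independent episodes between two hospitals. For the controlled pre/post contrast, 300 per site per period gives about 53–56% power, and 80% needs about 526–570, roughly double.

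This rests on 300 episodes in each of four cells, a common 36% in the three cells without intervention, no secular change, and independent episodes. The range reflects the choice of scale. Any positive clustering allowance lowers the power further. The power that the study will actually have cannot be judged until episode counts are known.

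**What to change.** 1. In *Analyses for objective 1*, define the 1a test as the site-by-period (intervention) term in the hierarchical model, with site and period in the model, so that it agrees with *Study design*.
2. In the sample-size paragraph, restate the requirement for that term: about 526–570 episodes per site per period for 80% power to detect an 11-point net reduction, before any clustering allowance. Equivalently, state 53–56% power at 300 per site per period, or a detectable net reduction of about 15 points. Name the scale used.
3. Show the figure at design effects of 1.0, 1.25 and 1.5, labelled as assumptions (arcsine power at 300 per cell of about 55%, 46% and 40%).
4. Replace the support from discharges and catheterized patients with year-1 bacteriuria episode counts at each site. Baseline surveillance already collects these.

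The cost is a rewrite of two paragraphs and a less favourable figure at 300. Data collection does not change and no extra recruitment is needed.
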